#### Outcomes

The dependent (outcome) variable is frailty, defined as “multi-systemic functional decline below a certain level, leading to increased vulnerability to a minor stressor with poor outcomes of disability and/or mortality” [16, 58]. The outcome will be expressed using three categories: non-frail, pre-frail, and frail when meeting 0, 1 or 2, and ≥ 3 criteria of the FRAIL scale. A larger total score indicates more a severely frail condition.

#### Statistical considerations

Descriptive results are expressed as mean and standard deviation (SD) or as number and percentage. Bivariate analyses will be performed using the χ^2^ test or Fisher’s exact test for qualitative variables and the Student *t-*test, analysis of variance (ANOVA), or Kruskal–Wallis test for quantitative variables. Logistic regression analysis will apply in variable selection and we used an entry criterion of *P* < 0.05. The data set will be divided into a training (70 %) and verification (30 %) set using random sampling. We will establish a frailty prediction model using the modeling data set, and discrimination will be expressed using area under the receiver operating curve and the Hosmer–Lemeshow test to evaluate goodness of fit [59]. As for internal validation, we will use a bootstrap technique with 1000 resamples from the training data set. The verification data set will be used for external verification, and its effectiveness evaluated according to accuracy and area under the receiver operating curve. All statistical analysis will be performed using Stata version 14 for Windows (Stata Corp, College Station, TX, USA). A *P* value of less than 0.05 will be considered statistically significant.

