#### Feasibility of recruitment and sample size

In the first stage, for the sample size required for modeling, we referred to the method of estimating sample size for multivariate logistic regression. For the categories with a smaller proportion of the outcome variables, the sample size should be at least 10 times the number of independent variables. There are two categories of dependent variables in this study (no frailty and frailty), and 20 important independent variables were initially estimated. Therefore, the sample size of the intervention group in this study is at least 200 patients. According to the literature data, the incidence of frailty in the older population with nutritional risk is approximately 26.5–54 % [18, 32, 34, 35]. Taking into account an expected incidence of 40 % and loss to follow-up of 10–20 %, we aim to include 600 patients. As for the total sample size, with reference to logistic regression modeling requirements, the modeling sample size is approximately two-thirds of the total sample size and the model verification sample size is approximately one-third of the total sample size. The total sample size is calculated to be at least 900 patients, of which at least 300 patients will be used for model verification.

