#### Definition of covariates

Potentially associated factors of frailty in the models included [16, 36–43] age, sex, ethnicity, education level, marital status, body mass index (BMI), living alone, living conditions, smoking, alcohol consumption, falling accidents in the past 12 months, immobilization for more than 4 weeks, polypharmacy, fatigue, resistance (ability to climb stairs), ambulation (ability to walk 100 m), illnesses (> 5), loss of more than 5 % body weight, nutritional risk, ADL, instrumental ADL, depression, cognitive function, handgrip strength, vision, hearing, sleeping, urinary function, and defecation function.

Age was grouped as 65–74 years old, 75–85 years old, and 85 years old and above. Ethnicity was categorized as Han and ethnic minorities. Education level was categorized as illiterate, primary school, junior high school, and high school and above. Marital status was categorized as married and divorced or widowed. Living alone was categorized as living alone or not living alone [40]. Living conditions was classified as living in a building with an elevator, a building without an elevator, or a bungalow. Polypharmacy was categorized as 0, 1–2, 3–4, 5–6, and more than 7 [16].

BMI was calculated as body weight divided by height (in meters) squared (kg/m^2^) [18] and was used to classify patients into groups of < 19 kg/m^2^, 19 to < 21 kg/m^2^, 21 to < 23 kg/m^2^, and ≥ 23 kg/m^2^. Participants’ weight in kg was measured to the nearest 0.1 kg using a digital electronic chair scale, and height (in cm) was measured to the nearest 1 mm using a stadiometer. Study participants were weighed while wearing light clothing and no shoes.

We referred to the FRAIL scale [38, 44], such as the items of fatigue, resistance (ability to climb stairs), ambulation (ability to walk 100 m), illnesses (> 5), and loss of more than 5 % body weight, which has been validated in Chinese older adults [45].

Nutritional risk was measured using the MNA-SF, a six-item scale with scores ranging from 0 to 14 points [19]. Patients were categorized into patients at risk of malnutrition (8–11 points) or malnourished (0–7 points) [39]. The MNA-SF has been validated in the Chinese population and has excellent test characteristics [10, 46].

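### Stage 1 lists P < 0.05 predictor selection before the 70/30 split and does not say the bootstrap repeats it, so both validation AUCs can be optimistic

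*Protocol article*

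**What the plan says.** The Stage 1 Statistical considerations section gives the modelling steps in this order:

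1. Selection: "Logistic regression analysis will apply in variable selection and we used an entry criterion of" P < 0.05. The data set used is not named.
2. Split: 70% training and a "verification (30 %) set using random sampling".
3. Model building: "We will establish a frailty prediction model using the modeling data set".
4. Internal validation: "we will use a bootstrap technique with 1000 resamples from the training data set".
5. Final check: "The verification data set will be used for external verification", judged by accuracy and AUC.

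The candidates are in Definition of covariates, in the list that begins "Potentially associated factors of frailty in the models included". It contains 29 variables. The Stage 1 sample size section worked with fewer: "20 important independent variables were initially estimated".

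**The concern.** Model building and the bootstrap are each tied to the training data; selection is not, and it comes before the split. Two separate problems can follow.

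- **Verification.** If all patients are used to screen the 29 candidates, a variable can enter partly because it happened to track frailty in the patients later set aside. The verification AUC then no longer comes from patients who played no part in building the model.
- **Bootstrap.** If each resample refits the coefficients of an already chosen set, the optimism correction covers coefficient estimation but not the choice among 29 candidates. This applies even when selection stays inside the training set.

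Both errors run upward, so two inflated figures could agree and look like mutual confirmation. These AUCs are the discrimination evidence Stage 1 offers before the model goes to the ward. The 30% set is a random part of the same data, so calling the check external adds weight that a leaked result would not deserve.

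**Working it through.** **The plan's own figures.** The sample size rule is "the sample size should be at least 10 times the number of independent variables", applied to the smaller outcome category.

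- 20 × 10 = 200 patients with the outcome; 200 / 0.40 = 500; 500 × 1.20 (20% loss) = 600 for modelling.
- 600 / (2/3) = 900 in total, leaving 300 for verification. The stated 600, 900 and 300 are reproduced.

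The documents give no AUC or optimism figure, so the size of the bias has to be simulated.

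**How much room selection has.** With no true association, 29 × 0.05 = 1.45 candidates pass by chance.

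- n = 900, 40% frailty: 900 × 0.70 × 0.40 = 252 training events; 252 / 29 = 8.7 per candidate.
- n = 3027, 40% frailty: 3027 × 0.70 = 2119; 2119 × 0.40 = 848 events; 848 / 29 = 29.2 per candidate.

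The bias should therefore shrink markedly at the enrolled size.

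**Simulation.**

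- From the documents: 29 candidates, P < 0.05, 70/30 split, n = 900 (planned minimum) and 3027 (enrolled), 40% frailty.
- Assumed: independent standard-normal candidates, univariable screening, none or 8 truly predictive, and 10% frailty as a sensitivity case.
- Signal strength is labelled by the best attainable AUC: weak about 0.60, moderate about 0.69, strong about 0.76.
- True AUC comes from 40,000 independent subjects. There were 120 replicates at n = 900 and 60 at n = 3027, with 15 resamples each. The standard error of the verification bias is 0.002 to 0.006.

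Bias = mean reported AUC − true AUC. Both bootstrap columns have selection inside the training set.

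| n, frailty | Signal | Verification, selection on all data | Verification, selection in training | Bootstrap, predictors fixed | Bootstrap, selection repeated |
|---|---|---|---|---|---|
| 900, 40% | none | +0.042 | −0.002 | +0.049 | +0.006 |
| | weak | +0.036 | −0.001 | +0.052 | +0.005 |
| | moderate | +0.012 | 0.000 | +0.021 | −0.010 |
| | strong | +0.004 | −0.001 | +0.005 | −0.013 |
| 3027, 40% | none | +0.026 | +0.002 | +0.028 | +0.004 |
| | weak | +0.005 | −0.003 | +0.013 | −0.005 |
| | moderate | −0.003 | −0.005 | +0.002 | −0.007 |
| | strong | −0.001 | −0.003 | +0.001 | −0.004 |
| 900, 10% | none | +0.073 | −0.005 | +0.075 | +0.014 |
| | weak | +0.071 | +0.010 | +0.094 | +0.020 |
| | moderate | +0.052 | +0.004 | +0.071 | +0.008 |
| | strong | +0.023 | +0.003 | +0.039 | −0.003 |
| 3027, 10% | none | +0.037 | −0.002 | +0.039 | +0.002 |
| | weak | +0.032 | +0.003 | +0.045 | +0.004 |
| | moderate | +0.008 | +0.002 | +0.019 | −0.002 |
| | strong | +0.003 | −0.001 | +0.006 | −0.005 |

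**Reading the table.**

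- Selection inside the training set removes the verification bias, to within about 0.010.
- The fixed-predictor bootstrap is optimistic without any leak into the verification set, so that part does not depend on the sentence order.
- Repeating selection leaves between −0.013 and +0.020. With stronger predictors it errs slightly low, which is the cautious direction.

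**Second design.** A separate simulation used 29 binary candidates, 10 of them real (assumed log odds ratios 0.2 to 0.9). At n = 900 and 40% frailty, the fixed-set bootstrap AUC was 0.687 against a true 0.674 (+0.013). With selection repeated it was 0.662 against 0.668 (−0.006). At n = 3027 the bias was about 0.005 at 40% frailty and 0.015 at 9%. The direction is the same and the size similar.

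**The case against.** **The order is inferred.** No sentence says selection precedes the split. Tense does not settle it, because the selection sentence itself mixes future and past, and building a model on the modelling data can be read as including the choice of predictors. This stands: a reader might infer that predictors were certainly chosen on the full data, and the document does not establish that.

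**Resampling only the training set is ordinary internal validation.** This also stands. The issue is only whether selection is repeated in each resample.

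**An article may leave such detail to the full plan.** This stands in part. But the section already fixes the threshold, the split, the number of resamples, the data they are drawn from and the performance measures. Carried out in the order given, those steps are a weaker procedure than an equally short alternative.

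**Extreme figures are not the document's.** If no candidate were related to frailty, full-data selection would give a verification AUC significantly above 0.5 in about 23 to 25% of studies, against 1.8% with training-only selection. A reader might conclude that the model may have no predictive ability. The documents do not support that. The candidates come from cited frailty literature, the plan specifies no test of AUC against 0.5, and frailty near 10% appears nowhere (the plan gives 26.5 to 54% and expects 40%).

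**Stage 2 is a safeguard.** It evaluates the model prospectively and excludes patients used in development, so a Stage 1 leak cannot enter its results. This stands, although the Discussion concedes that the Stage 2 sample is not large enough.

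**Conclusion.** The concern holds as a weakness in how the steps are ordered and specified, not as proof that the reported performance will be false. As written, the section permits a verification set that helped choose the predictors and a bootstrap that ignores selection.

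- At the planned n = 900 and 40% frailty, the possible bias is about 0.00 to 0.04 AUC for verification and 0.005 to 0.05 for a fixed-predictor bootstrap.
- At the enrolled 3027 with moderate or strong predictors it is about 0 to 0.01. It is larger only if predictors are weak or frailty is much rarer than planned; for example, +0.019 for the fixed bootstrap with moderate predictors and 10% frailty.

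These sizes rest on assumed predictor strengths, independent candidates and univariable screening. The entry criterion could equally mean stepwise entry, which these runs do not cover. The correction is worth making because it is the right step under either reading of the text and needs no new data.

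**What to change.** In the Stage 1 Statistical considerations section:

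1. Put the random split first.
2. State that P < 0.05 selection uses the training set only.
3. Apply the model to the verification set once, with predictors and coefficients frozen.
4. State that each of the 1000 resamples repeats the full selection from all 29 candidates, and report the optimism-corrected AUC and calibration slope.
5. If selection has already been run on the full data, redo it in the training set.

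The cost is wording, computing time and a slightly less favourable reported AUC.

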Frailty is a complex, age-related clinical condition characterized by a decline in physiological capacity across several organ systems, and it is a state of increased vulnerability to stress [9, 22, 24]. However, older adults with frailty have an increased likelihood of unmet care needs, falls and fractures, hospital readmissions, increased length and cost of hospital stay, lower quality of life, iatrogenic complications, and early mortality [10, 24]. This increased risk of adverse clinical outcomes can occur even without the presence of comorbidities [24, 25].

The investigation of frailty has attracted enormous scientific interest in the past few years as it affects multiple domains of human functioning, including nutritional status, cognitive function, gait, mobility, balance, muscle strength, endurance, and activities of daily living (ADL) [26]. Additionally, previous reports have suggested that the attributes of frailty are multidimensional and that its definition should comprise nutrition, cognition, mentality, and other aspects [27–30]. Identification is a critical step in the intervention or management of frailty [24, 29, 30]. Both the cycle of frailty model [22] and the integral conceptual frailty model [31] include nutrition as a factor to explain frailty. However, undernutrition is considered a sub-factor in physical frailty in the integral conceptual frailty model and a predisposing factor for frailty in the cycle of frailty model [22]. Previous studies have mainly investigated the relationship between undernutrition and frailty [9, 21, 32, 33], but none have reported the degree of influence on frailty according to nutritional risk, despite nutritional risk being a modifiable variable.

Using the current study protocol, in the first stage of this study, we used data from a cohort study to develop an early warning model of frailty based on nutritional risk screening. In the second stage of the study, we report the prevalence of frailty among older inpatients with nutritional risk and apply the frailty early warning model in the clinic to screen high-risk patients and provide corresponding intervention target information.

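### Stage 1 picks predictors from 29 candidates at an unadjusted P < 0.05, and none of the stated checks would show that a factor offered as an intervention target entered by chance

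*Protocol article*

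**What the plan says.** All of this is in the protocol article, mostly in its account of Stage 1.

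- *Definition of covariates* opens its list with "Potentially associated factors of frailty in the models included" and then names 29 factors, with literature references. Five of them (fatigue, resistance, ambulation, illnesses, weight loss) are the items of the FRAIL scale, which also defines the outcome.
- *Statistical considerations* gives the selection rule: "Logistic regression analysis will apply in variable selection and we used an entry criterion of" P < 0.05. It does not say whether selection is univariable, forward, backward or from one full model. It mentions no shrinkage, penalty or adjustment.
- The same section splits the data 70/30. It judges the model by AUC and the Hosmer–Lemeshow test, and the verification set by accuracy and AUC. For internal validation it says "we will use a bootstrap technique with 1000 resamples from the training data set". It does not say whether selection is repeated in each resample.
- *Background*, like the Abstract, states the purpose: to "apply the frailty early warning model in the clinic to screen high-risk patients and provide corresponding intervention target information".

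**The concern.** The model has two uses, and they need different evidence. Screening needs a risk score that ranks and calibrates well in new patients, and the stated checks are aimed at that. Pointing to intervention targets relies on individual factors, and no stated check looks at those one at a time. A noise factor that slipped in at P < 0.05 would barely move the AUC, so good validation results would say nothing about whether that factor belongs.

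What is at stake is that clinicians could be directed to a factor such as sleeping, alcohol or hearing that was retained by chance. Selecting on a threshold also tends to exaggerate the retained coefficients and the training-set AUC. How much that matters here depends on the number of events.

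**Working it through.** **The plan's own figure.** *Feasibility of recruitment and sample size* says "20 important independent variables were initially estimated" and asks for ten patients in the smaller outcome category per variable. So 10 × 20 = 200 events; 200 / 0.40 = 500 patients; 500 × 1.2 = 600 for modelling; 600 / (2/3) = 900 in total. Both stated figures, 600 and 900, are reproduced. The rule counts 20 variables, whereas the covariate list has 29.

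**Size of the training set.** The population section reports 3027 enrolled, and 0.70 × 3027 ≈ 2119. At the expected 40% incidence that is about 848 events, or 848 / 29 ≈ 29 per candidate factor.

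**Chance of at least one false entry.** With k truly unrelated candidates tested independently at 0.05 (two-sided assumed), the chance is 1 − 0.95^k and the expected number is 0.05k. The documents do not give k, so a range is shown. The correlated columns come from 200,000 simulated sets of equally correlated tests.

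| k null factors | Expected false entries | Independent | r = 0.2 | r = 0.4 | r = 0.6 |
|---|---|---|---|---|---|
| 5 | 0.25 | 23% | – | – | – |
| 10 | 0.50 | 40% | 38% | 32% | 25% |
| 14 | 0.70 | 51% | 47% | 39% | 30% |
| 20 | 1.00 | 64% | 59% | 49% | 36% |
| 29 | 1.45 | 77% | 71% | 58% | 42% |

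With 13 null factors the independent figure is 48.7%, so 14 is the smallest number that passes one half.

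**Overfitting.** This is an illustrative simulation. Assumptions: 10 real predictors with log-odds 0.3 per SD, 19 noise factors, correlation 0 or 0.2, backward selection at P < 0.05. Each setting was run twice, with 150 training sets per run. Incidences of 5% and 10% are assumptions and do not appear in the documents. The gap is apparent AUC minus AUC in new patients.

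| Training set, incidence | Any noise factor kept | Apparent v new AUC, correlation 0 | Apparent v new AUC, correlation 0.2 | Gap | Calibration slope (one run) |
|---|---|---|---|---|---|
| 600, 40% | 63–75% | 0.739 v 0.708; 0.744 v 0.710 | 0.831 v 0.807; 0.829 v 0.805 | 0.024–0.034 | 0.83–0.87 |
| 2119, 5% | 56–69% | 0.755 v 0.711; 0.757 v 0.711 | 0.856 v 0.837; 0.857 v 0.828 | 0.019–0.046 | 0.79–0.85 |
| 2119, 10% | 61–67% | 0.750 v 0.726; 0.749 v 0.731 | 0.845 v 0.837; 0.847 v 0.834 | 0.008–0.024 | 0.91–0.94 |
| 2119, 40% | 55–69% | 0.735 v 0.726; 0.735 v 0.726 | 0.827 v 0.820; 0.827 v 0.821 | 0.006–0.009 | 0.96 |

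The share of models keeping a noise factor is close to 1 − 0.95^19 = 62% in every row. A larger sample shrinks the AUC gap but leaves the false-entry rate where it was.

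**The case against.** A reader might infer that at least one spurious target is more likely than not. The documents do not support that. The 77% needs all 29 candidates to be null and their tests independent. Five of the 29 are components of the outcome scale and cannot be treated as null, though that overlap is a separate matter. The rest come from the literature. Age, sex, ethnicity and education cannot be intervention targets even if they enter by chance. Removing those nine leaves 29 − 9 = 20. Even if all 20 were null, the chance is 64% with independent tests, 49% at r = 0.4 and 36% at r = 0.6. The 55–75% in the simulation follows from its assumed 19 noise factors, a number with no source in the article.

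Nor does the article say that factors enter one at a time, since the procedure is not specified. It says that applying the model will yield target information, not that every retained factor becomes a target.

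It is also fair to say that optimism is partly dealt with. The 30% verification set gives an honest AUC, and Stage 2 excludes the patients used in development. At the plan's own figures (2119 patients, 40% incidence) the AUC gap is below 0.01, and coefficients of retained real predictors were inflated by only 1–2%. Whether the bootstrap repeats the selection may be settled in an analysis plan that is not shown. Family-wise error control is not a usual requirement for choosing predictors.

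One part of the point is left standing. The entry rule is a stated choice, the target-finding purpose is stated, and every stated check is on whole-model performance.

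**Conclusion.** The point holds in a limited form. The flat P < 0.05 rule, with checks confined to overall performance, does not support reading an individual retained factor as an intervention target. About 5% of truly unrelated candidates will enter whatever the sample size. The probability of at least one false entry runs from 23% (5 null) through 40% (10 null) to 64% (20 null) with independent tests, and is lower with correlation. No single figure can be fixed, because the documents do not give the number of null factors.

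Overfitting is a secondary issue. It is negligible if the training set is about 2119 and incidence is near 40%. It matters more, roughly 0.02 to 0.04 in AUC (0.046 in one run) with calibration slopes of about 0.8 to 0.87, only with the planned 600 patients or an incidence far below the assumed 40%. These sizes rest on the simulation's assumed effects and its use of backward selection. The change is worth making because it costs little; the point does not undermine the design.

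**What to change.** In *Statistical considerations* for Stage 1:

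1. Name the selection procedure, and state that the whole selection step is repeated inside each of the 1000 bootstrap resamples already planned.
2. Report the optimism-corrected AUC and calibration slope, and apply the resulting shrinkage factor to the coefficients before the model goes into Stage 2. Penalised logistic regression is an acceptable alternative, not a requirement.
3. Report how often each candidate factor is retained across the resamples.
4. State that retained modifiable factors are hypothesis-generating candidates, not established intervention targets.

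A Bonferroni threshold (0.05 / 29 = 0.0017) is not the remedy. It would limit chance entries, but a predictive association would still not show that changing the factor changes frailty. Inclusion frequencies and shrinkage do not show that either, which is why item 4 is needed.

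The cost is extra computing and a few sentences, with no new data. The downside is a slightly lower reported AUC and a more cautious list of targets.

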## Abstract

**Background:**

Previous reports suggest that the attributes of frailty are multidimensional and include nutrition, cognition, mentality, and other aspects. We aim to develop an early warning model of frailty based on nutritional risk screening and apply the frailty early warning model in the clinic to screen high-risk patients and provide corresponding intervention target information.

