#### Population and inclusion and exclusion criteria

In the first stage of modeling, participants must meet the following criteria: having no frailty according to the FRAIL (Fatigue, Resistance, Ambulation, Illnesses, & Loss of Weight) scale (scores from 0 to 2), malnourished or at risk of malnutrition according to the Mini-Nutritional Assessment-Short Form (MNA-SF; scores range from 0 to 11), and written informed consent provided by patients enrolled in this study.

Exclusion criterion were as follows: patients with frailty at the time of enrollment; patients who are persistently unconsciousness or unable to provide informed consent for participation, or their caregivers were unable to provide effective information; patients who were initially admitted to the intensive care unit (ICU) [13]; patients with anorexia nervosa, acute pancreatitis, acute liver failure, cystic fibrosis, stem cell transplantation, severe chronic gastrointestinal diseases, acute infectious diseases or chronic wasting diseases at enrollment; and patients who were lost to follow-up or had died at the 30-day of follow-up. A total of 3027 patients were enrolled in the current study.

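### The P < 0.05 entry rule gives nutritional risk no exemption, so the model can lose its only adjusted estimate of how the grade of nutritional risk influences frailty

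*Protocol article*

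**What the plan says.** The Abstract states the aim: "We aim to develop an early warning model of frailty based on nutritional risk screening". The Background adds that earlier work has not shown how strongly nutritional risk influences frailty, although nutritional risk can be modified.

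First-stage eligibility requires patients to be "malnourished or at risk of malnutrition according to the Mini-Nutritional Assessment-Short Form (MNA-SF; scores range from 0 to 11" points. Under Definition of covariates, the list that begins "Potentially associated factors of frailty in the models included" runs from age to defecation function and includes "loss of more than 5 % body weight, nutritional risk, ADL, instrumental ADL, depression, cognitive function, handgrip strength". The nutritional-risk candidate is binary: "Patients were categorized into patients at risk of malnutrition (8–11 points) or malnourished (0–7 points").

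Statistical considerations gives one selection rule for the whole list: "Logistic regression analysis will apply in variable selection and we used an entry criterion of" P < 0.05. The general significance level is the same: "A *P* value of less than 0.05 will be considered statistically significant". The article does not say whether entry means univariable screening or a stepwise procedure. It does not say that any candidate is forced in or kept regardless of its P value.

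**The concern.** The selection rule and the stated purpose do not fit together. For prediction alone, a weak term can reasonably be dropped. This study also justifies itself by the influence of nutritional risk on frailty, and it promises information on targets for intervention. A rule that treats nutritional risk like any other candidate cannot guarantee an adjusted estimate of that influence.

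If the term does not enter, the final model has no coefficient for malnourished versus at-risk patients. The second stage would then apply a model that does not distinguish these two grades through the MNA-SF category. A small odds ratio with a narrow confidence interval would tell the reader something about the question raised in the Background. A term missing from the model would not.

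**Working it through.** **Count of candidates.** The list under Definition of covariates has 29 entries. Nutritional risk is the 19th, so 28 others fall under the same rule.

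**The plan's own sample size.** 20 variables × 10 events = 200 events, and 200 / 0.40 = 500 patients. Allowing for loss, 500 / 0.90 = 556 and 500 / 0.80 = 625. The stated 600 lies between these, and 600 / (2/3) = 900 in total. So 600 is a planning minimum for modelling. The same article reports 3027 patients enrolled and a 70% training set: 0.70 × 3027 ≈ 2119. The figures below use 2119, on the assumption that all 3027 are available for analysis.

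**Chance that the term misses P < 0.05.** Inputs:

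- n = 2119 (from the article, as above).
- Frailty incidence e = 0.40 (the article's expected value; its literature range is 26.5–54%).
- Share malnourished p = 0.30 (assumed; not in the article).
- Two-sided test (assumed; the article does not say).
- R² = share of the term's variance explained by the other candidates, 0 or 0.3 (assumed).
- Odds ratio for malnourished versus at risk, 1.3, 1.5 or 2.0 (assumed).

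Formulas: SE(log OR) = 1 / √[n · p(1−p) · e(1−e) · (1−R²)], and P(not entered) ≈ Φ(1.96 − ln OR / SE).

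R² = 0: n · p(1−p) · e(1−e) = 2119 × 0.21 × 0.24 = 106.8, so SE = 0.0968.

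- OR 1.3: 0.2624 / 0.0968 = 2.71; Φ(−0.75) = 0.23.
- OR 1.5: 0.4055 / 0.0968 = 4.19; Φ(−2.23) = 0.01.

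R² = 0.3: 106.8 × 0.7 = 74.8, so SE = 0.1157.

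- OR 1.3: 0.2624 / 0.1157 = 2.27; Φ(−0.31) = 0.38.
- OR 1.5: 0.4055 / 0.1157 = 3.51; Φ(−1.55) = 0.06.

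At OR 2.0 the probability is about 0 in both cases.

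**Range over the article's own incidence figures**, same formulas, n = 2119:

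| Incidence | n·p(1−p)·e(1−e) | OR 1.3 (R² 0 to 0.3) | OR 1.5 (R² 0 to 0.3) |
|---|---|---|---|
| 26.5% | 2119 × 0.21 × 0.1948 = 86.7 | 0.31–0.47 | 0.03–0.12 |
| 40% | 106.8 | 0.23–0.38 | 0.01–0.06 |
| 54% | 2119 × 0.21 × 0.2484 = 110.5 | 0.21–0.36 | 0.01–0.05 |

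**If only the planned minimum of 600 were modelled** (40% frail): 600 × 0.21 × 0.24 = 30.24 and SE = 0.182 at R² = 0. Non-entry is then 0.70 at OR 1.3 and 0.39 at OR 1.5. At R² = 0.3 the values are 0.77 and 0.54. These are not the main figures, because 3027 patients are reported as enrolled.

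**Is a modest effect plausible?** The article gives one indication. The cross-sectional community study cited in the Background reports odds ratios for frailty of 3.72 (malnutrition) and 3.66 (malnutrition risk). If both share one reference group, which is assumed, the implied ratio for malnourished versus at risk is 3.72 / 3.66 ≈ 1.02. The first interval is wide (1.40 to 9.94) and the setting differs, so this does not estimate the effect in inpatients. It shows only that the article gives no reason to count on a large one.

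**The case against.** The strongest objection is that nutritional risk defines the population. Every first-stage patient has an MNA-SF score of 0–11, and the second stage carries the same criterion over. A reader might infer that a model without the term would no longer be based on nutritional risk screening. The article does not support that, because eligibility alone keeps the model one for patients with nutritional risk. This part of the objection stands. What can be lost is the contrast within that population.

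Three other strong readings also fail:

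- *Competition with BMI and weight loss would push the term out.* The entry procedure is not stated. Under univariable screening there is no such competition, and the R² = 0 figures are the relevant ones. If there is overlap, BMI and weight loss could still carry nutritional information into the model.
- *No estimate at all would be reported.* The same section plans χ² or Fisher tests for qualitative variables, so an unadjusted association would still be examined. Only the adjusted estimate is at risk.
- *Non-entry would be read as no influence.* Nothing in the article says so.

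It is also fair to say that a prediction model may drop a term that adds nothing, and that an article with no analysis plan at hand may leave retained covariates to that plan. The first argument is weakened by the Background, which asks about influence as well as prediction. The second does not remove the point, because the article does state a selection rule, and as written that rule covers nutritional risk.

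**Conclusion.** The point holds in a limited form. As written, the entry rule can delete the only adjusted estimate of how the grade of nutritional risk influences frailty, and the article gives that influence as the gap in earlier work. It does not undermine the model's population, its eligibility or the design.

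At the article's expected 40% incidence and about 2119 training patients, non-entry has probability about 0.23–0.38 at an odds ratio of 1.3, 0.01–0.06 at 1.5, and about 0 at 2.0. Omission is a real risk for a modest effect and unlikely for a strong one. The malnourished share of 30%, the odds ratios, the shared variance of up to 30% and the two-sided test are assumptions that the article does not supply. A much lower frailty incidence, such as 10%, would raise the probabilities but lies outside the article's 26.5–54% range and is not relied on here. This is a worthwhile, cheap improvement.

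**What to change.** State that the MNA-SF category (0–7 versus 8–11) stays in the model whatever its P value, and that the P < 0.05 entry rule applies only to the other 28 candidates. Report its adjusted odds ratio with 95% CI in all cases. Add that this contrasts malnourished with at-risk patients and has no well-nourished reference, so it does not measure the effect of nutritional risk against good nutrition.

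The cost is one sentence in the plan and one parameter in the model. The stated sample size does not change. The downside is a slight loss of parsimony if the term adds nothing to prediction. If the sponsor intends nutritional risk to define the population only, the plan should say so, and the Background should not present its degree of influence as a question the model will answer.
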